### Characteristics and health status of each group

2.12

In order to verify whether or not statistical differences in characteristics and/or health status exist among treatment group 1, treatment group 2, and the control group, we will calculate the average, standard deviation, minimum value and maximum value for continuous data, and we will compare the average values for the three groups by using the t-test. For the purpose of group comparisons, we will use the chi-squared test or Fisher's exact test for categorical data.

### Analysis of first outcome variables

2.13

Descriptive statistics (number in each group, average, standard deviation, minimum value and maximum value) will be used for each variable affecting the DCR (CR, PR, and SD), and the results for the two test groups and the control at the last visit versus the results at baseline will be presented. The statistical significance of any difference found between test groups and the placebo group will be analyzed using chi squared test. If any difference among three groups (2 test groups and 1 placebo group) is found, Bonferroni or Duncan method will be used. Chi squared test between placebo group and treatment group 1, placebo group and treatment group 2 will be additionally conducted.

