### Outcome measures

2.6

The primary outcome is a comparison of the disease control rates (DCR) among treatment groups 1 and 2 and the control group after 12 weeks compared to baseline, which will be assessed from the date of randomization to 12 weeks, as determined by chest X-ray, CT or MRI according to the RECIST criteria.^[11]^

The secondary outcomes are comparisons of the complete response (CR) and the partial response (PR) to the treatment, the stability of the disease (SD), progression free survival (PFS), time to progression (TTP), and tumor marker (CEA, NSE) and WBC differential count (LMR, NLR) and natural killer cell activity and QOL (EORTC QLQ-C30) among treatment groups 1 and 2 and the control group after 6 weeks and 12 weeks compared to baseline.

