### Randomization and blinding

2.8

After informed consent has been obtained, random assignment will be performed by using a computer-generated, blocked, random-allocation sequence with a 1:1:1 ratio. Each participant will be assigned to a group according to a pre-generated randomization table and an assigned randomized number. Each participant will be assigned to treatment group 1, treatment group 2, or the control according to the allocation codes of the randomized assignment method, which will be prepared in advance. In order to maintain a double-blind trial, we will use the same formulations and properties for the placebo so that it is indistinguishable from the test drug. The allocation of unique codes for each group will be managed by the managing pharmacist, will be kept in a sealed envelope, and will not be disclosed until the end of the clinical trial.

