### Sample size calculation

2.9

The sample size was determined by considering the number of participants available, the minimum range of the efficacy assessment, and the expected dropout rate during the study period. When the first two factors were considered, the total number of participants required for each group was calculated as 15, for a total of 45. When a dropout rate of 30% was used for each group, the required number of participants was calculated as 22 (15/(1 – 0.3) = 21.43 ≒ 22). Thus, when all factors are considered, the number of participants to be registered for each group is 22, so a total of 66 patients will be recruited.

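### The primary DCR test chain names a procedure for means (Duncan) with no rule for choosing it over Bonferroni, then adds two dose-versus-placebo tests with no stated gate or adjusted level

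*Protocol article*

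**What the plan says.** The endpoint is a rate. In section 2.6 (Outcome measures): "The primary outcome is a comparison of the disease control rates (DCR) among treatment groups 1 and 2 and the control group".

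Section 2.13 (Analysis of first outcome variables) sets three steps in this order:

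1. "The statistical significance of any difference found between test groups and the placebo group will be analyzed using chi squared test".
2. "If any difference among three groups (2 test groups and 1 placebo group) is found, Bonferroni or Duncan method will be used".
3. "Chi squared test between placebo group and treatment group 1, placebo group and treatment group 2 will be additionally conducted".

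Step 2 carries a condition. Step 3 does not, and no level is attached to it. Section 2.14 repeats the chain for the secondary outcomes.

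No significance level or sidedness appears anywhere in the article. Allocation is 1:1:1 (section 2.8). Section 2.9 gives the arm sizes: "the total number of participants required for each group was calculated as 15, for a total of 45", raised to 22 per arm for dropout. The Methods part of the abstract calls the trial exploratory, and section 2.11 rules out interim analyses.

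**The concern.** There are three problems, and the first two do not depend on any calculation.

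- **The method does not fit the endpoint.** Duncan's test ranks group means after an analysis of variance. It is not a follow-up to a chi-squared comparison of proportions.
- **The choice is open.** Two analysts could each follow section 2.13 faithfully, one with Bonferroni and one attempting Duncan, and report different conclusions on the primary endpoint.
- **The added tests bypass the correction.** If the two control comparisons are run whatever the global test shows, and each at the full level, the correction in the preceding sentence protects nothing.

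A significant comparison of one dose with placebo is the result most likely to be quoted and to guide the choice of dose. A reader needs to know what error rate stands behind it.

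**Working it through.** **Plan's own figure.** 15/(1 − 0.3) = 21.43, rounded up to 22 per arm; 3 × 22 = 66. This reproduces. The 15 itself cannot be checked, because no level, power or expected DCR is given.

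**Inputs.** Three equal arms (section 2.8); n = 15 evaluable or 22 enrolled per arm (section 2.9). *Assumed, not in the document:* two-sided 5% for each test, Pearson chi-squared without continuity correction, and the same true DCR in all arms, taken from 0.50 to 0.95.

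**Large samples.** Two independent tests would give 1 − 0.95² = 9.75%. The two comparisons share the placebo arm, so with equal arms their statistics have correlation 0.5, and 1 − P(|Z₁| < 1.96, |Z₂| < 1.96) = 0.0907, or about 9.1%. By symmetry, false benefit for at least one dose is about 4.5%, against 2.5% for a single comparison.

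**Exact enumeration at the planned sizes.** With a and c responders in a dose arm and the placebo arm, the pairwise statistic is 2n(a − c)² / [(a + c)(2n − a − c)], compared with 3.84. The global statistic is n Σ(pᵢ − p̄)² / [p̄(1 − p̄)], compared with 5.99 on 2 degrees of freedom. Summing the binomial probabilities over all outcomes gives, in %:

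| n per arm | True DCR | Either control comparison significant | Either comparison or global test significant | False benefit, either dose |
|---|---|---|---|---|
| 15 | 0.50 | 8.21 | 9.07 | 4.11 |
| 15 | 0.60 | 8.72 | 9.59 | 4.47 |
| 15 | 0.70 | 9.90 | 10.83 | 5.05 |
| 15 | 0.80 | 8.97 | 9.81 | 4.50 |
| 15 | 0.85 | 7.50 | 8.60 | 3.69 |
| 15 | 0.90 | 4.55 | 6.48 | 2.15 |
| 15 | 0.95 | 0.90 | 2.91 | 0.39 |
| 22 | 0.50 | 8.89 | 9.80 | 4.45 |
| 22 | 0.60 | 8.46 | 9.43 | 4.24 |
| 22 | 0.70 | 8.67 | 9.53 | 4.43 |
| 22 | 0.80 | 9.24 | 10.05 | 4.75 |
| 22 | 0.85 | 9.31 | 10.22 | 4.77 |
| 22 | 0.90 | 7.95 | 9.28 | 3.93 |
| 22 | 0.95 | 2.69 | 5.11 | 1.22 |

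**Sensitivity to the test used.** With a continuity correction or Fisher's exact test, either control comparison is falsely significant in at most 4.5% of trials. Continuity-corrected pairwise tests plus the global test reach at most 5.9%.

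**What a rule would restore.**

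- Each comparison at 2.5% (Bonferroni): 4.6% in large samples; exact values at most 4.4% (n = 15) and 4.5% (n = 22).
- Each at 5%, only after a significant global test: at most 4.4% at either size. For example, at n = 22 and DCR 0.85 the 9.31% splits into 3.61% with a significant global test and 5.70% without. The gate removes the second part.

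**The case against.** **The wording of the third step is ambiguous.** It follows directly on the conditional sentence, so it could merely identify which comparisons Bonferroni is meant to cover. That reading cannot be excluded. It is the less natural one, because the tests are described as additional and carry no condition, but the text does not call them primary evidence either.

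**The 5% is not the document's.** This stands. Every percentage above is conditional on that assumed level and on uncorrected Pearson tests. The latter is the natural reading, since section 2.12 offers Fisher's exact test for group characteristics and section 2.13 does not, but it remains a reading.

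**The two-sided figure overstates the chance of the claim that matters.** This stands in part. The 7.5 to 10% includes trials in which a dose looks worse than placebo. False benefit is about 4 to 5%, still roughly 1.5 to 2 times the 2.5% of one comparison.

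**The trial is exploratory and dose-finding.** This also stands: strict familywise control is not required. It does not excuse naming a method that cannot be applied to the endpoint.

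A reader might infer several stronger things, which the article does not support:

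- *That the sponsor may pick among routes after seeing the data.* The article says nothing of the kind. An analysis plan may settle the choice before unblinding, allocation codes stay sealed until the end (section 2.8), and there is no interim analysis.
- *That the error rate is uncontrolled.* Under the stated assumptions it does not exceed about 11%.
- *That Bonferroni after a global test is a mistake.* It is conservative, not wrong.

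**Conclusion.** The point holds as a defect in how the primary analysis is specified. Section 2.13 names one option that does not apply to a proportion, gives no rule for choosing between the two options, and adds control comparisons whose gate and level are unstated. This is a stated rule that does not work, not a detail left to another document.

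The size is conditional. For uncorrected Pearson tests at an assumed two-sided 5% and a common true DCR of 0.50 to 0.85, at least one control comparison is falsely significant in about 7.5 to 10% of trials, or up to about 11% if the global test also counts as a positive result. The excess shrinks or vanishes at a DCR of 0.90 to 0.95 with 15 per arm and at 0.95 with 22 per arm, and the pairwise excess does not arise with continuity-corrected or Fisher tests. It would therefore be wrong to state as a fact that the error rate is doubled.

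The change should be made, but given the exploratory purpose it is not a fatal flaw.

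**What to change.** In section 2.13:

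1. Delete Duncan and the choice it creates.
2. State the significance level and sidedness.
3. Fix one rule for the two dose-versus-placebo comparisons: either each at half the level (Bonferroni, which the section already names), or each at the full level only after a significant global test, which is a closed procedure for three groups.
4. Report both DCR differences with 95% confidence intervals whatever the tests show, and label any pairwise result outside the rule as descriptive.

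Neither rule is always more powerful. With illustrative DCRs of 0.70 (placebo), 0.85 and 0.95 and 22 per arm, the chance of showing benefit for at least one dose is about 49% with the gate and 53% with Bonferroni; other scenarios slightly favour the gate. Bonferroni is the smaller edit.

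The cost is about two sentences. The downside is that a dose-versus-placebo difference significant only at the unadjusted level, or only without the gate, could not be claimed.

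This wording should not be copied into section 2.14. That section covers tumour markers, cell ratios, quality of life and time-to-event outcomes, where a rule written for a difference in proportions does not fit and where Duncan is not ruled out on the same ground for continuous means.

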### Analysis of second outcome variables

2.14

Descriptive statistics (number in each group, average, standard deviation, minimum value and maximum value) will be used to describe differences in the CR, PR, SD, PFS, TTP, tumor marker (CEA, NSE), WBC differential count (LMR, NLR), natural killer cell activity and QOL (EORTC QLQ-C30) between the two test groups and the control, and any differences between either of the two test groups and the control at the last visit versus baseline will be presented. The statistical significance of any difference found between test groups and the placebo group will be analyzed using chi squared test. If any difference among three groups (2 test groups and 1 placebo group) exist, Bonferroni or Duncan method will be used. Chi squared test between placebo group and treatment group 1, placebo group and treatment group 2 will be additionally conducted. The statistical significance of any variable in any group will be tested by using the paired *t* test or the Wilcoxon signed rank test.

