### Principles of interpretation of results

2.11

The main analysis will be the FAS group analysis for the validity evaluation. The PP group analysis will be carried out separately to evaluate whether or not any differences from the FAS analysis results exist. For the FAS group, if a defect value happens at any point or a dropout occurs before the clinical trial ends, the most recent data will be analyzed as if it were obtained at that point in time (Last Observation Carried Forward Analysis). The SG analysis will be conducted to assess safety. All statistical analyses will be performed with SPSS version 21.0; no interim analyses will be performed.

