## Discussion

3

Afatinib is an available drug that is administered orally. It is an ErbB family blocker that, in comparison with the first-generation EGFR-TKIs, irreversibly and selectively blocks signaling from all homodimers and heterodimers formed by EGFR and by the erb-b2 receptor tyrosine kinase 2 (HER2/ERBB2), HER3/ERBB3, and HER4/ERBB4 receptors.^[13,14]^ Recently, three studies on the role of afatinib have been published: a combined analysis of LuxLung 3 and 6^[15]^ and analyses of LuxLung 7^[16]^ and LuxLung8.^[17]^ In LuxLung 3 and 6, afatinib showed superiority over the first-generation EGFR-TKIs: only afatinib among EGFR-TKIs improved the overall survival in comparison with the platinum-based chemo doublet. In LuxLung 7, afatinib was compared with gefitinib in a phase 2 B, open-label, randomized, controlled trial of EGFR mutation-positive NSCLC in treatment-naive patients and showed significant improvement in progression-free survival (PFS) and time-to-treatment failure. In LuxLung 8, afatinib was compared with erlotinib in a phase 3, open-label, randomized, controlled trial involving patients with a stage IIIB or IV squamous cell carcinoma who had progressed after at least four cycles of platinum-based chemotherapy and who had shown significant improvements in PFS and OS. Despite remarkable outcome results, patients receiving EGFR-TKIs usually developed secondary resistance after approximately 9 to 13 months (median PFS: 9–12 months) and showed major adverse events grade 3 or higher, including diarrhea, rash or acne, and stomatitis or mucositis.^[16–18]^

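### PFS and TTP are to be described by average, SD, minimum and maximum, although under the plan's own figures most of the averaged times would not be progression times

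*Protocol article*

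**What the plan says.** Section 2.14 (Analysis of second outcome variables) sets one description for every secondary outcome: "Descriptive statistics (number in each group, average, standard deviation, minimum value and maximum value) will be used to describe differences in the CR, PR, SD," and the list continues with PFS, TTP, the tumour markers, the remaining markers and quality of life. PFS and TTP thus stand in one list with tumour markers and cell counts.

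For the same list, the between-group rule is "The statistical significance of any difference found between test groups and the placebo group will be analyzed using chi squared test". The within-group rule begins "The statistical significance of any variable in any group will be tested by using the paired" and names the paired t test or the Wilcoxon signed rank test.

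The only rule for incomplete follow-up is in section 2.11 (Principles of interpretation of results). For a missing value or a dropout in the full analysis set, "the most recent data will be analyzed as if it were obtained at that point in time (Last Observation Carried Forward Analysis". The article mentions no censoring, Kaplan-Meier estimate or log-rank test.

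Three other places matter. Section 2.6 places the secondary outcomes at 6 and 12 weeks. Section 2.9 plans for early loss: "When a dropout rate of 30% was used for each group". The Discussion gives the expected course on EGFR-TKIs: "secondary resistance after approximately 9 to 13 months (median PFS: 9–12 months".

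**The concern.** A mean and SD require one completed time per patient. Take three patients: one progresses at week 6, one leaves progression-free at week 6, and one is progression-free at week 12. If follow-up times are averaged as they stand, they contribute 6, 6 and 12 weeks. Only the first value is a PFS time; the other two are lower bounds.

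What is at stake is the reported size of any difference in PFS or TTP. If dropout times are averaged, the figure depends on how many patients leave early as well as on how fast they progress. A better significance test would not repair this, because the description itself would still be wrong. The tests named are unsuitable too: chi-squared ignores time and censoring, and PFS and TTP have no baseline value for a paired test.

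**Working it through.** **The plan's own figure.** Section 2.9: 15/(1 − 0.30) = 21.43, rounded up to 22 per arm; 3 × 22 = 66. This reproduces.

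**Inputs from the article.** Median PFS 9–12 months (Discussion), assessments at 6 and 12 weeks (2.6), dropout 30% and 22 patients per arm (2.9).

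**Assumptions.** PFS is exponential. Observation ends at week 12. A fraction d of patients drop out, uniformly over 0–12 weeks and independently of progression. One month is 4.348 weeks.

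**Step 1: hazard and 12-week quantities, median 9 months.**
- λ = ln 2/(9 × 4.348) = 0.01771 per week
- Progression-free at week 12: S = exp(−12λ) = 0.809
- Mean of min(T, 12), no dropout: R = (1 − S)/λ = 10.81 weeks
- Mean of min(T, C) for a dropout: D = 1/λ − (1 − S)/(12λ²) = 5.60 weeks

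For a 12-month median, S = 0.853 and R = 11.09 weeks. Expected progressions per arm without dropout are 22 × 0.191 = 4.2 and 22 × 0.147 = 3.2.

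**Step 2: what share of the averaged times are progressions?** The share is (1 − d)(1 − S) + d(1 − R/12). At d = 0.30:
- median 9 months: 0.70 × 0.191 + 0.30 × 0.099 = 0.16
- median 12 months: 0.70 × 0.147 + 0.30 × 0.076 = 0.13

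So about 84% to 87% are dropout or week-12 times. Exponential dropout reaching 30% by week 12 gives progression shares of 16.2% and 12.5%, the same picture.

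**Step 3: the mean under two readings, median 9 months.**
- Dropout times averaged as they stand: (1 − d)R + dD.
- Dropouts carried forward to 12 weeks: (1 − d)R + dL, where L = 12 − ∫₀¹²(12 − t)(1 − t/12)λe^(−λt)dt = 11.19 weeks.

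| Dropout | Times as they stand | Carried to 12 weeks |
|---|---|---|
| 0% | 10.81 | 10.81 |
| 15% | 10.03 | 10.87 |
| 30% | 9.25 | about 10.9 |
| 45% | about 8.5 | 10.98 |

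On the first reading, 30% dropout lowers the mean by 10.81 − 9.25 = 1.56 weeks. With equal hazards, 15% against 45% dropout gives 0.30 × (10.81 − 5.60) = 1.56, a false difference of about 1.6 weeks. On the second reading the gap is 10.98 − 10.87 = 0.11 weeks.

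**Step 4: scale of a real effect.** Without dropout, halving the hazard (median 18 months) moves the mean from 10.81 to 11.38, or 0.57 weeks.

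**Step 5: sensitivity.**
- Exponential dropout: 9.15 weeks at 30%, and 1.78 weeks for 15% against 45%.
- Progression dated only at scans in weeks 6 and 12 (assumed), patients without a scan left out: 10.96 − 9.83 = 1.1 weeks for the same imbalance, and 11.69 − 11.39 = 0.3 weeks for a halved hazard.
- Progressors only, 30% exponential dropout: a mean of 5.4 to 5.5 weeks for medians of 9 to 12 months. That says almost nothing about PFS.

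**The case against.** The case on the other side is substantial, and much of it stands.

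- **The text does not say that censored times count as progressions.** A reader might infer this from the mean, but it is an inference. The sentence is a blanket template that also covers response categories, for which an SD or a minimum has little meaning. With visits at weeks 6 and 12 and a chi-squared test, it could describe progression status at each visit, an average then being a proportion. That reading would rescue the test only by making PFS and TTP something other than times, and carrying status forward would still count unobserved time as progression-free.
- **The large false difference depends on how dropouts are handled and on an imbalance.** Section 2.9 plans the same 30% in each group, and equal dropout with equal hazards gives no difference between arms. The 15% against 45% split is an assumption, and carry-forward almost removes its effect. It would therefore be too strong to say that the mean measures dropout rather than progression.
- **The 12-week cap is not a fault in itself.** Without dropout, the capped mean is the 12-week restricted mean: valid, though insensitive. Setting 10.8 weeks against a 39-week median compares two different quantities.
- **Use of the result.** A reader might infer that mean PFS would settle the dose. Nothing in the article says so; DCR is primary, and PFS and TTP are two of many secondary outcomes in an exploratory trial.
- **End of observation and analysis set.** Section 2.2 mentions a follow-up period without defining it, and the schedule table is not shown. Longer follow-up would raise the share of progressions, but a plain mean would still ignore censoring. The full analysis set requires a measurement of the primary outcome, so some very early dropouts would not be averaged; the scan-dated figures allow for this.

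The central point remains: the article states a summary for PFS and TTP that does not suit incomplete follow-up, and each way of carrying it out that was examined has a defect. Because the method is stated, this is not a detail left to an analysis plan that is not shown.

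**Conclusion.** The concern holds in limited form and is worth correcting. Average, SD, minimum and maximum do not describe PFS or TTP when, under exponential PFS and observation ending at week 12, over 80% of the times would not be progressions.

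The direction of the error depends on a choice that the article leaves open. Dropout times averaged as they stand bias the mean downward, by about 1.6 weeks at the planned 30% dropout and a 9-month median. Carry-forward biases it slightly upward (about 10.9 against 10.81 weeks), because unobserved time is treated as progression-free. A false difference between arms of about 1.6 weeks needs both the first reading and the assumed dropout imbalance; it is an illustration, not a prediction.

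The weak response of the mean to a real effect comes mainly from the 12-week window and the few events, and is not a separate error.

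**What to change.** In section 2.14, take PFS and TTP out of the variables described by average, SD, minimum and maximum. In section 2.11, exempt them from last observation carried forward. State instead:

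- the number of events per arm;
- Kaplan-Meier progression-free probabilities at weeks 6 and 12 per arm, with 95% confidence intervals, and the differences from control;
- censoring of progression-free patients at their last tumour assessment;
- an exploratory log-rank comparison for these two variables, in place of the chi-squared and paired tests.

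The cost is a few lines of text, with no new patients or assessments. There will be no single mean PFS figure, and intervals will be wide with about 3 to 4 events expected per arm. For a halved hazard, about 81% against 90% progression-free at week 12 with 22 per arm and no dropout, the 95% interval for the difference is 1.96 × √(0.81 × 0.19/22 + 0.90 × 0.10/22), roughly ±21 percentage points. The change removes the dropout bias, provided that dropout is unrelated to progression. It does not make a 12-week window more sensitive.

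### Section 2.14 compares arms on continuous secondary outcomes by mean change to last visit with a chi-squared test, with no baseline covariate and no week-6 arm comparison

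*Protocol article*

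**What the plan says.** Section 2.6 of the protocol article lists the secondary outcomes and sets their timing: they are compared "among treatment groups 1 and 2 and the control group after 6 weeks and 12 weeks compared to baseline".

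Section 2.14 then says how they are analysed.

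- **Summary.** "Descriptive statistics (number in each group, average, standard deviation, minimum value and maximum value) will be used to describe differences in the CR, PR, SD". The list runs on through PFS and TTP to "tumor marker (CEA, NSE), WBC differential count (LMR, NLR), natural killer cell activity and QOL (EORTC QLQ-C30) between the two test groups and the control".
- **Contrast.** "any differences between either of the two test groups and the control at the last visit versus baseline will be presented".
- **Between-group test.** "The statistical significance of any difference found between test groups and the placebo group will be analyzed using chi squared test". A Bonferroni or Duncan step follows if the three groups differ, with further chi-squared tests of each dose against placebo.
- **Within-group test.** Changes inside a group "will be tested by using the paired *t* test or the Wilcoxon signed rank test".

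Section 2.11 adds that, in the full analysis group, when a value is missing or a participant drops out, "the most recent data will be analyzed as if it were obtained at that point in time (Last Observation Carried Forward Analysis". Section 2.9 plans 22 patients per group so that 15 remain after 30% dropout.

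**The concern.** The article is explicit here. It fixes a summary, a contrast and a test for six continuous outcomes, and each has a problem.

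1. **Test.** Chi-squared compares frequencies. It cannot be applied to a marker level, a ratio or a QOL score unless the outcome is first cut into categories, and no cut is given. The Duncan step compares means, so it does not match a chi-squared test either.
2. **Baseline.** It serves only as the value subtracted. With random allocation, subtraction over-corrects unless the correlation between baseline and follow-up is close to 1, and this adds noise.
3. **Week 6.** Section 2.6 declares it a comparison time point, but section 2.14 presents the arms only at the last visit. In that contrast, week 6 can appear only when a dropout's value is carried forward as if it were the final one.
4. **Summary.** Means, SDs and extremes describe positive, right-skewed quantities poorly. With 15 to 22 patients per arm, a few very high values can drive a mean change.

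At stake is how much the trial can say about either dose from its continuous efficacy data, and whether the week-6 comparisons promised in 2.6 are ever made.

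**Working it through.** **The plan's own figure.** 15/(1 − 0.3) = 21.43, rounded up to 22 per group; 3 × 22 = 66. This reproduces section 2.9 and is not in dispute. Section 2.9 gives no alpha, power, effect or SD, so everything below rests on assumed values.

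**Sections side by side.**

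| Item | 2.6 | 2.14 |
|---|---|---|
| Arm comparison at week 6 | yes | none |
| Arm comparison at week 12 | yes | last visit |
| Role of baseline | reference | reference, and within-group paired tests |
| Between-arm test | not stated | chi-squared |

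If the planned dropout occurs, up to 22 − 15 = 7 patients per arm could enter the last-visit contrast with an earlier value.

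**Baseline subtracted or adjusted for.** Let σ² be the variance, assumed equal at baseline and follow-up, and ρ their correlation.

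- Variance of change: 2(1 − ρ)σ²
- Variance after adjustment: (1 − ρ²)σ²
- Ratio: (1 + ρ)/2, so the saving is (1 − ρ)/2

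| ρ (assumed) | Change | Adjusted | Ratio | Saving |
|---|---|---|---|---|
| 0.3 | 1.40 | 0.91 | 0.65 | 35% |
| 0.5 | 1.00 | 0.75 | 0.75 | 25% |
| 0.7 | 0.60 | 0.51 | 0.85 | 15% |
| 0.9 | 0.20 | 0.19 | 0.95 | 5% |

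At ρ = 0.5, 15 patients act like 15/0.75 = 20. The formula uses variances and correlation only, so it does not depend on skew.

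**Using week 6.** If the effect is averaged over weeks 6 and 12, with the same correlation between all pairs of visits, the adjusted variance is ((1 + ρ)/2 − ρ²)σ². Relative to change at one visit the ratio is 0.40, 0.50, 0.60 and 0.70 for ρ = 0.3, 0.5, 0.7 and 0.9. This applies to the averaged effect. For a week-12 contrast, week 6 helps mainly for patients who lack a week-12 value.

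**Scale.** Simulation of a log-normal marker in two arms: true halving of the geometric mean, ρ = 0.5, two-sided 5%.

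| n per arm | log-SD | t-test, raw change | t-test, log change | log ANCOVA |
|---|---|---|---|---|
| 22 | 0.5 | 90% | 99.5% | 99.9% |
| 22 | 0.6 | about 75% | 96% | 99% |
| 22 | 1.0 | 28% | 62% | 73% |
| 22 | 1.5 | 10% | 32% | 39% |
| 15 | 1.0 | 21% | 45% | 56% |

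Repeat runs differ by two or three percentage points. A rank test on raw change at 22 per arm and log-SD 1.0 gives 41%, between the raw t-test and the log analyses.

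**Influence of single patients.** At 22 per arm, the most extreme patient supplies a median 42% (log-SD 1.0) to 55% (log-SD 1.5) of an arm's sum of squares for raw change. The figure is 29% at log-SD 0.5 and 22% for normal data.

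**The case against.** **It is analysis-plan detail.** Log transformation, covariates and visit terms for secondary outcomes of an exploratory trial are often left to the full protocol or SAP, neither of which is shown. If 2.14 had been silent, that would settle the matter. It is not silent: it states a summary, a contrast and a test, and the contrast disagrees with 2.6. What stands is that the full documents may already be better.

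**The power loss is not the plan's.** This stands. Section 2.14 names no t-test on change, so 28% is the power of a benchmark and not of the stated method. A log-normal marker with a multiplicative effect also favours the log analysis by construction, and most of the simulated gain comes from that step.

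**Baseline and week 6 are used.** A reader might infer that both are discarded. The text does not support that. Baseline is the reference for change and enters the paired tests, and week 6 can enter through last observation carried forward. The supported statement is narrower: baseline is not a covariate, and week 6 has no arm comparison in 2.14.

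**Extreme values need not dominate.** A reader might infer that a few patients drive every outcome whichever test is used. That goes too far. No scale is stated, so a raw scale is inferred from the absence of any transformation. A rank test would limit the influence of outliers, although the Wilcoxon option in 2.14 works only within groups. The article gives no distributions, and skew is not shown for QOL or natural killer cell activity.

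**Conclusion.** The point holds in limited form. Two parts need no outside assumption: sections 2.6 and 2.14 disagree on week 6, and the only between-arm test named for six continuous outcomes does not fit them. A third is a clear improvement on a stated method: baseline adjustment saves 5% to 35% of variance for ρ from 0.9 to 0.3, given equal variances at the two times.

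The benefit of a log scale is plausible for CEA, NSE, LMR and NLR, but its size is unknown. Under the assumed log-normal halving at 22 per arm and ρ = 0.5, it ranges from large (28% against 73% at log-SD 1.0) to moderate (about 75% against 99% at log-SD 0.6). These figures are illustrative. They do not show that the plan gives away most of the precision in these data, and they say nothing about QOL.

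The change is worth making, but these are secondary outcomes of an exploratory trial and the primary analysis is not affected.

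**What to change.** Rewrite the continuous-outcome part of section 2.14 so that it agrees with 2.6.

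- **Model.** Analyse each of CEA, NSE, LMR, NLR, natural killer cell activity and QOL in one baseline-adjusted model (mixed model or ANCOVA) with arm, visit (weeks 6 and 12), arm-by-visit and the baseline value. In the mixed model, keep each value at the visit where it was measured, and say so against the carry-forward rule in 2.11.
- **Contrast.** Report each dose against placebo at week 12 with a 95% CI, and show week 6 from the same model.
- **Scale.** Use logs for CEA, NSE, NLR and LMR, and for natural killer cell activity if it proves skewed, reported as geometric-mean ratios. Keep QOL on its own scale as a mean difference.
- **Summaries.** Give medians and quartiles for the skewed markers and ratios.
- **Test.** Drop chi-squared for these outcomes.

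The cost is revised wording and slightly more analysis work, using standard models available in SPSS 21, the software named in 2.11. No patients, visits or measurements are added. The one trade-off is that marker results become ratios rather than differences.
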